**Table 3 Tab3:** **Information to be collected and used in analysis**

	**Baseline**	**3 Months**	**12 Months**
**Patient Characteristics**			
Basic sociodemographics: age, sex, race, ethnicity, preferred language to use, living situation, education, health literacy	X		
Marital status, employment status, income	X	X	X
Acculturation: place of birth, parent and grandparent place of birth, length of time in US	X		
Executive Cognitive Function (FAB)	X		
Stroke, HTN and hospitalization history; co-morbidities (modified Charlson)	X	X	X
**Clinical and functional outcomes**			
**Primary outcome**			
Blood pressure measurement	X	X	X
**Secondary outcomes**			
Cost-effectiveness	X	X	X
Health-related quality of life (EuroQol)	X	X	X
ADL/Functional Status (modified Barthel/Rankin for patient self-report)	X	X	X
Physical function (PROMIS®)	X	X	X
New cardiovascular events		X	X
**Exploratory outcome mediators**			
Knowledge of HTN management	X	X	X
Stroke literacy questions (Willey)	X	X	X
Adherence to regimen (Morisky)	X	X	X
Beliefs about medications (BMQ)	X	X	X
Linkage to PCP	X	X	X
Chronic condition management (PACIC)	X	X	X
General self-efficacy scale (Lorig)	X	X	X
Lifestyle management: diet/sodium intake (modified CATCH), physical activity (IPAQ), tobacco, alcohol and drug use, body mass index	X	X	X
Depression (PROMIS®)	X	X	X
Medication profile	X	X	X
**Organizational and system costs**			
Intervention costs: nurse practitioner and health coach time, patient educational material		X	X
Home care-related costs: nurse, therapy, social work, and aide home care visits		X	X
Overall medical costs: nights in hospital, ED visits, physician visits, medications		X	X

Notes: Barthel/Rankin [37,53]; FAB = Frontal Assessment Battery [54]; Charlson, modified self-report [55,56]; EuroQol [38]; PROMIS® [57]; Willey [58]; Morisky, 8-item version [59]; BMQ [60], PACIC = Patient Assessment of Chronic Illness Care, modified subscales [61]; Lorig [62]; CATCH [63]; IPAQ = International Physical Activity Questionnaire [64,65]; PROMIS® depression [66]; ED = emergency department; ADL = activities of daily living; PCP = primary care provider; HTN = hypertension.

### Primary outcome: change in systolic blood pressure

The primary outcome is change in SBP from baseline to 3 and 12 months. As with the baseline interview, patients are assessed with a validated, automated oscillometric BP device (Microlife Watch BP, Golden, CO, USA). The average of the BP measurements from the two enrollment screening visits will be used for comparative analysis to the follow up measurements. At the 3- and 12-month follow up evaluations, the BP will be measured by interviewers, blinded to group assignment, 3 times on the dominant arm identified at baseline and the average will be used for analysis.

### Secondary outcomes: cost-effectiveness, patient function, and quality of life

Costs will focus on direct costs including costs of the interventions, home care utilization, hospital and emergency department use, outpatient visits and medication regimens. Patient function and health-related quality of life will be assessed with a modified self-report Barthel Index [37] and the EuroQol [38]. See Table 3.

### Exploratory outcomes: moderators and mediators

Data are being collected so that moderators and mediators that may affect treatment outcomes can be explored. Moderators include race and ethnicity (that is black/Hispanic) differences and baseline HTN severity (for example, Stage 1 (SBP = 140 to 159 mmHg) versus Stage 2 (SBP ≥ 160 mmHg)). Mediators include changes in health behaviors (for example, diet, physical activity, weight loss, medication adherence) and antihypertensive medication intensification.

### Statistical analysis plan

#### Data analyses for primary outcome: SBP

The main hypothesis is that those assigned to the intervention groups will, on average, exhibit greater 3-month and 12-month decreases in SBP than those assigned to the usual care condition. The primary proposed analyses will use mixed random effects models, and a full information maximum likelihood (FIML) approach, with sensitivity analyses using generalized estimating equation (GEE) regression models. The change from pre- to post-treatment values of SBP will be modeled as functions of time, treatment and the interaction of time and treatment. The general longitudinal mixed effects model, using SAS PROC MIXED (SAS, Cary, NC, USA), will be used to model serial correlations and group heterogeneity in residual variances if needed. The intent-to-treat (ITT) analyses will permit all individuals with at least one observation to be included. If a non-linear pattern of change is observed, non-linear models will be used in sensitivity analyses.

Prior to analyses, baseline values of all variables will be examined in order to determine if any covariates require modeling due to imbalance among groups. Examination of baseline differences on key variables between completers and those lost to follow up will be conducted to inform about the nature of the missing data.

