### Interventions

#### Nurse Practitioner (NP) Arm

The study’s NPs are employed by a professional practice group affiliated with the parent home health organization. The practice group provides primary and specialty medical services and care coordination and can bill third parties. The intervention, which complements UHC, builds on an existing 30-day transitional care program established in the practice group. Program components are modeled after two evidence-based models: 1) the Transitional Care Model (TCM) developed and validated for HF patients [26], which uses an advanced practice nurse for intervention activities, and 2) the Four Pillars of the 30-day Care Transitions Intervention® (CTI) [30], which emphasizes patient self-management. Both models have demonstrated effectiveness in reducing hospital readmissions [25,31]. Because the intervention commences only after a patient is admitted to home care, we have omitted the element that calls for visiting the patient in the hospital before discharge. This element has been omitted in other tests of the TCM [32]. We also have modified the traditional TCM in at least two other ways: 1) to allow for the inclusion of at-risk eligible patients referred to home care from community physicians, and 2) to increase the emphasis on stroke recurrence prevention - specifically on reducing SBP. We incorporated and combined the goal of improved transitional care with the goal of effective chronic disease self-management. The program length of 30 days was chosen because it is the allowable Medicare reimbursable timeframe for transitional care services and thus should contribute to the sustainability of the model after the grant period ends.

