#### NP + health coach (HC) Arm

This arm, like the NP-only arm, complements UHC. It is designed so that all patients receive the intensive 30-day NP intervention as described above plus an additional 60 days of collaboration and self-management support from a specially trained HC. The HC joins the NP at the third patient intervention visit and subsequently provides 3 in-home visits and 3 telephone calls for HC/patient-caregiver collaboration. The planned schedule of NP/HC contacts is outlined in Table 1.

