#### Power for SBP rate of change

Power was calculated, examining the rate of change, including all three waves in the analyses. The following assumptions were used: R = 0.90 (reliability); pooled σ = 20.75; δ = 5, 6, 7 (SBP point reduction per year in the intervention groups relative to the UHC group reduction); d = δ/σ (where δ is point reduction per year and d is Cohen’s d for the rate of change); ρ = 0.6 is the average correlation between baseline and follow up assessments; Tn = 3 time points (baseline, 3 month and 12 month). The formulas from Diggle, Liang and Zeger (1994) were used [39]: the power calculation demonstrates that under ITT, we can detect a rate of reduction in SBP equivalent to 5.40 mmHg which translates to relatively small effect sizes using Cohen’s d. It is also noted that the assumed standard deviation was conservatively posited to be quite large (pooled estimate of around 21). If a smaller standard deviation is observed, power will be greater. Thus, a sample size of 165 per group was proposed.

For the non-linear, longitudinal change sensitivity analyses [40], the assumptions were the same as above, and an endpoint reduction in SBP of 6 points was posited. Assuming a non-linear decline function and differential treatment effects, power was greater than 0.80 to detect small effects (for example, a 0.5 point reduction) in one intervention group at 3 months and medium to large effects (2.5 to 5 point reduction in SBP) in the second group at 3 months, with a net reduction of 6 points by study end in both groups.

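### The power calculation allows for no clustering by nurse practitioner or health coach, and the published primary model names no provider effect, although only the intervention arms are treated by study providers

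*Protocol article*

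**What the plan says.** **Primary model.** Under Data analyses for primary outcome: SBP, the protocol article proposes mixed random effects models fitted by full information maximum likelihood, with GEE as a sensitivity analysis. The mean structure is given as "The change from pre- to post-treatment values of SBP will be modeled as functions of time, treatment and the interaction of time and treatment". The dependence it mentions is serial correlation and, if needed, residual variances that differ by group. It does not list the random effects.

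**Power.** Under Power for SBP rate of change, the inputs are a reliability of 0.90, "pooled σ = 20.75", yearly differences of 5, 6 and 7 mmHg, "ρ = 0.6 is the average correlation between baseline and follow up assessments", and three time points (baseline, 3 and 12 months). The only correlation is within patient. The section reports a detectable 5.40 mmHg and concludes: "Thus, a sample size of 165 per group was proposed". Methods/Design says that the trial is powered for each intervention against UHC.

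**Delivery.**
- Nurse Practitioner (NP) Arm: the study's "NPs are employed by a professional practice group affiliated with the parent home health organization".
- NP + health coach (HC) Arm: "all patients receive the intensive 30-day NP intervention as described above plus an additional 60 days" of support from a trained coach.
- Randomization and blinding: the UHC nurse is told how to reach the transitional care NP on that patient's case.
- Intervention fidelity monitoring protocol: coaches record encounters with a fifth of their own patients, are scored on counselling technique and receive feedback.
- Setting: study site: UHC goes to every arm.

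**The concern.** Patients who share an NP or coach may have correlated outcomes, because delivery depends on individual skill: tailoring a plan, problem solving, motivational interviewing. The protocol itself monitors coaches' performance. This dependence is added in the intervention arms only, so the design is partially nested.

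Neither serial correlation within a patient nor a group-specific residual variance represents covariance between two patients of the same provider. A GEE clustered on the patient does not either. If that covariance is positive and left out, the variance of an intervention-arm mean change is too small. Intervals for NP versus UHC and NP + HC versus UHC are then too narrow, and the test rejects too often. The same omission makes the stated detectable difference optimistic.

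**Working it through.** **Step 1: reproduce 5.40 mmHg.** The section does not state alpha, sidedness or target power for this figure. I assume two-sided 5% and 80%, so the multiplier is 1.96 + 0.84 = 2.80. For a comparison of slopes between independent patients:

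detectable difference = 2.80 × √[2σ²(1 − ρ) / (n × SSx)]

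- Actual times 0, 0.25 and 1 year: the mean is 0.4167 and SSx = 0.1736 + 0.0278 + 0.3403 = 0.5417. With σ² = 20.75² = 430.56, σ²(1 − ρ) = 172.2. Then √[2 × 172.2 / (165 × 0.5417)] = 1.963, and the detectable difference is 5.50. Power at 5.40 is 78.5%.
- Variance multiplied by the reliability 0.90, with SSx = 0.5 (equal spacing or two points): the detectable difference is 5.43. Power at 5.40 is 79.6%.

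So the stated figure is reached, to within 0.03 to 0.10 mmHg, with no design effect. It leaves no room for clustering.

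**Step 2: add clustering in the intervention arm only.** With k providers per arm and equal caseloads m = 165/k:

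- design effect in the intervention arm: DE = 1 + (m − 1) × ICC
- variance ratio of the contrast with UHC: V = (DE + 1)/2
- true type I error of a nominal 5% test: 2[1 − Φ(1.96/√V)]
- detectable difference: 5.40 × √V
- power at 5.40, taken as 80% without clustering: Φ(2.80/√V − 1.96)

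The ICC here is that of the SBP change. Neither k nor the ICC is in the article, so both are assumptions.

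| k | m | ICC | DE | √V | Type I error | Detectable (mmHg) | Power at 5.40 |
|---|---|---|---|---|---|---|---|
| any | any | 0 | 1.00 | 1.000 | 5.0% | 5.40 | 80% |
| 15 | 11.0 | 0.01 | 1.10 | 1.025 | 5.6% | 5.53 | 78% |
| 8 | 20.6 | 0.02 | 1.39 | 1.094 | 7.3% | 5.91 | 73% |
| 15 | 11.0 | 0.05 | 1.50 | 1.118 | 8.0% | 6.04 | 71% |
| 4 | 41.25 | 0.05 | 3.01 | 1.416 | 16.6% | 7.65 | 51% |

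The last row in full: DE = 1 + 40.25 × 0.05 = 3.01; V = 4.01/2 = 2.01; √V = 1.416; 1.96/1.416 = 1.384, giving 16.6%; 5.40 × 1.416 = 7.65.

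**Step 3: sensitivity.** Starting from the reproduced 5.50 instead of 5.40, the range is 5.64 to 7.79 mmHg. With 20 providers and ICC 0.01 the standard error rises by only about 2%. With 3 providers and ICC 0.05 it rises by 53%. The formula treats one level of provider; in NP + HC, NP and coach clustering could both contribute.

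**The case against.** Four arguments carry weight.

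1. *The model is judged on silence.* A reader might infer that the primary analysis treats all patients as independent. The article does not support that: it proposes random effects without listing them, and a full analysis plan could include a provider term. This stands for the model. It does not help the power calculation, whose inputs are listed.

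2. *The error is conditional.* A reader might conclude that the standard errors are too small and that type I error exceeds 5%. That needs an ICC above zero and inference beyond the trial's own providers. If the intervention works through no provider at all, this source of clustering disappears; inflation arises under a null where providers differ but average to no effect. Inference conditional on the present staff is a legitimate alternative. However, the NP arm section wants the model sustained after the grant, which points to inference beyond them.

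3. *The size is assumed.* No passage places the trial within the range, and none shows that an ICC of 0.05 for SBP change would persist to 12 months after a 30-day NP programme. This stands. The power section also calls its standard deviation conservative. In the middle case, a true value of 20.75/1.094 = 19.0 would restore the power, but it would not correct the type I error.

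4. *Some delivery facts are inferred.* One NP pool across both arms is a fair reading but is not stated, so it cannot be asserted that a strong or weak NP team moves both contrasts together. Coaches serve NP + HC only. Staff enter every encounter in the electronic record, so provider identity is probably recoverable, but the article does not say so.

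**Conclusion.** The point holds in conditional form. It is firm that the stated power inputs include no provider ICC or design effect, and that 5.40 mmHg is what an independent-patient formula yields. It is also firm that the published model names no provider effect and that the dependence it does name would not capture one, in a design where only intervention patients have study providers.

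Whether standard errors are understated depends on a positive ICC for SBP change. Under the assumed 4 to 15 providers per arm and ICC 0.01 to 0.05, type I error would be about 5.6% to 16.6%, the detectable difference about 5.5 to 7.7 mmHg, and power at 5.40 mmHg about 78% to 51%. The low end is nearly negligible and the high end serious; the article cannot say which applies. This merits a change to the plan, but it does not show the primary analysis to be invalid.

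**What to change.** - **Model.** Pre-specify a partially nested mixed model for the SBP change: an NP random effect in the two intervention arms, a coach random effect in NP + HC, and UHC patients as singletons, with small-sample degrees of freedom such as Kenward-Roger. Make it at least a sensitivity analysis to the primary model.
- **Few providers.** If there are too few providers to estimate the variance stably, run the same model over fixed ICCs, for example 0.01, 0.02 and 0.05.
- **Patients with no encounter.** Assign them to the provider allocated to them, so that the intention-to-treat set stays whole. Confirm that allocated and treating provider are recorded.
- **Power.** State the number of NPs and coaches and an assumed ICC. Present 5.40 mmHg as holding only with no provider clustering, beside the range under those assumptions.

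The sample size does not change. The cost is analysis wording, one or two variance components, somewhat wider intervals and a less favourable stated detectable effect. No new patients or outcome data are needed.

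### The primary SBP model takes its covariates from observed baseline imbalance and does not plan baseline adjustment, so the model is not fixed in advance and gives up about 15 to 20% of variance on the plan's own assumptions

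*Protocol article*

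**What the plan says.** The Protocol article, under *Data analyses for primary outcome: SBP*, proposes a mixed random effects model fitted by full information maximum likelihood, with GEE as a sensitivity analysis. Change in SBP is to be "modeled as functions of time, treatment and the interaction of time and treatment". No other term is named.

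The same section then gives a rule for covariates: before analysis, "baseline values of all variables will be examined in order to determine if any covariates require modeling due to imbalance among groups". It names no covariate and states no threshold or test for imbalance.

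*Power for SBP rate of change* gives the figures needed to size the point: "pooled σ = 20.75" and "ρ = 0.6 is the average correlation between baseline and follow up assessments". It uses three waves, at baseline, 3 and 12 months, with 165 participants per group, and states that "we can detect a rate of reduction in SBP equivalent to 5.40 mmHg".

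**The concern.** There are two linked problems.

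- **The selection rule.** Under randomisation any baseline difference between arms is chance. The reason to adjust for a variable is that it predicts the outcome, and imbalance says nothing about that. Because the rule covers every baseline variable and gives no criterion, two analysts following it could fit different primary models to the same trial.
- **Baseline SBP.** It is measured in everyone and is assumed to correlate 0.6 with follow-up, so it is the obvious prognostic variable. Under the text as written it gets no adjustment unless it happens to look imbalanced.

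At stake are precision and a primary model that is fixed in advance. The planned effects are 5 to 7 mmHg, so a change of about half a mmHg in the detectable difference is worth having when the data are already collected.

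**Working it through.** **Inputs from the article:** σ = 20.75 mmHg, ρ = 0.6, n = 165 per arm, visits at 0, 0.25 and 1 year.

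**Assumptions:** two-sided alpha of 0.05 (the article states no alpha) and 80% power (the article gives 0.80 only for the non-linear sensitivity case), so the multiplier is 1.96 + 0.84 = 2.80. No dropout. Compound symmetry, with equal SDs at baseline and follow-up unless noted.

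**1. The plan's own figure.** The longitudinal slope formula gives a detectable difference of 2.80 × √[2σ²(1 − ρ)/(n·Sxx)].
- Mean time is 0.4167, so Sxx = 0.1736 + 0.0278 + 0.3403 = 0.5417.
- Variance = 2 × 430.56 × 0.4/(165 × 0.5417) = 3.854, and the detectable difference is 2.80 × 1.963 = 5.50 mmHg.
- Power at 5.40 mmHg is 78.5%, and 172 per arm would be needed for 80%.
- The article does not say how its reliability of 0.90 enters. Using σ√0.90 with equally spaced visits gives 5.43 mmHg.

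The stated 5.40 is thus reproduced closely, and it is reached without any baseline adjustment.

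**2. Change contrast at one visit (3 or 12 months).**
- Unadjusted: 2σ²(1 − ρ) = 0.80σ², SD 18.56. Detectable difference 2.80 × √(2 × 0.80 × 430.56/165) = 2.80 × 2.043 = 5.72 mmHg.
- Adjusted for baseline SBP: σ²(1 − ρ²) = 0.64σ², SD 16.60. Detectable difference 2.80 × 1.828 = 5.12 mmHg.
- Ratio: 0.64/0.80 = (1 + ρ)/2 = 0.80, a 20% reduction.
- Power at 5.40 mmHg: 75.3% unadjusted, 84.0% adjusted. Number per arm for 5.40 mmHg: 186 against 149.

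A generalised least squares calculation with baseline as a response wave gives the same 0.80 when free baseline means in each arm are compared with a common baseline mean. The loss is therefore the same whether baseline is subtracted or modelled as the first wave with free means.

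**3. Three-wave linear slope, the quantity the trial was powered on.**
- Free baseline means: variance 3.854, detectable difference 5.50 mmHg.
- Common baseline mean: variance 3.280, detectable difference 2.80 × 1.811 = 5.07 mmHg.
- Ratio: 3.280/3.854 = 0.851, a reduction of about 15%.

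**4. Effect of selecting on baseline SBP.** Eligibility requires SBP of at least 140 mmHg at two visits. Selecting on baseline narrows its spread but leaves the regression slope of follow-up on baseline at 0.6 and the residual variance at 0.64σ². Let baseline variance be kσ².
- Change-score variance becomes [0.64 + (1 − 0.6)²k]σ² = (0.64 + 0.16k)σ².
- As an example, suppose selection lowers the correlation to 0.4. Then 0.36k/(0.36k + 0.64) = 0.16, so k = 0.339.
- Ratio: 0.64/(0.64 + 0.16 × 0.339) = 0.64/0.694 = 0.92, a reduction of about 8%.
- Truncating a normal distribution at 140 and 200 mmHg, with SD 20.75 and an assumed unselected mean of 130 to 150, gives ratios of 0.94 to 0.90.

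**The case against.** **The best defence** is that a condensed article need not give the full parameterisation. The section admits anyone with at least one observation, and the power calculation counts baseline among its three time points. Baseline SBP is therefore most plausibly a response wave, not merely something subtracted. If the mixed model then held baseline means equal across arms, there would be no loss at all. It is true that baseline is probably a response wave, and this shapes the fix. But the article states no such constraint, and with free baseline means the loss is the same 20% for a visit contrast. The covariate rule, moreover, is not an omitted detail: it is stated, and it is the part that should go.

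Several stronger readings are tempting but not supported:

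- **That the covariates are chosen post hoc.** A reader might infer that outcomes influence the choice. The check precedes analysis and uses baseline values only. It is data-dependent, and no type I error inflation has been shown.
- **That the unadjusted estimate is biased.** A baseline difference of one standard error, 20.75 × √(2/165) = 2.28 mmHg, would move a change-score estimate by (1 − 0.6) × 2.28 = 0.91 mmHg. Over randomisations this averages to zero. It is the source of the extra variance, (1 − 0.6)²σ² = 0.16σ², and not a further harm. The imbalance rule might also pick up such a difference.
- **That selection at 140 mmHg makes the loss larger.** Putting a lower correlation into (1 + ρ)/2 suggests so (0.70 at ρ = 0.4), but that formula needs equal SDs. Selection on baseline breaks this and shrinks the gain.
- **That screening will almost surely flag something.** The article gives no test or level. Table 3 has 20 rows marked at baseline, several plainly correlated, so no false-flag probability can be calculated.
- **That the sample size is undermined.** The 5.40 mmHg figure does not rely on adjustment.

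**Conclusion.** The point holds as one of precision and prespecification. The primary model is left to depend on chance baseline imbalance, and baseline SBP has no planned adjustment. The variance forgone is 20% for the 12-month change contrast and about 15% for the slope, given ρ = 0.6, equal SDs, compound symmetry and no dropout. The detectable differences also assume two-sided 0.05 and 80% power. The real gain could be under 10% if eligibility screening narrows the baseline SD. The comparison stays valid without the change, which is nonetheless worth making because it costs almost nothing.

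**What to change.** Remove the imbalance-driven rule from the primary analysis and replace it with a model fixed in advance:

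- Keep baseline, 3- and 12-month SBP as responses and constrain the baseline mean to be common across the three arms. This suits the likelihood approach already chosen and keeps participants who have only a baseline value.
- Alternatively, model 3- and 12-month SBP with baseline SBP as a covariate. With complete data this gives the same precision for the visit contrasts.
- Name any further prognostic covariates before baseline data are compared by arm, choosing them for their expected relation to SBP and from data already collected.
- Report baseline tables descriptively, with no role in model selection.

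The cost is a sentence or two of analysis text. No new data, visits or participants are needed.
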